#### Sociodemographic - and other variables

Age, sex, living arrangements, educational level, previous falls, home care services, medication list, date of hip fracture, and type of operation are variables that are collected at baseline. Information about number of falls, readmission to hospital, and mortality are also registered at discharge from the nursing homes, at 3 and 12 months after surgery.

### Adherence to the program

To ensure adherence to the program, a physiotherapist employed in the project will educate and motivate the nursing staff in the nursing homes in the functional training group. The nurses will register in a log when they have performed the functional training, at least 4 times a day. Additionally, the accelerometer registration will reveal the activity level in both groups.

### Adverse advents

Adverse events are registered in the following 4 categories: falls, cardiovascular events, musculoskeletal injuries and health care utilization [42]. Furthermore, number of scheduled training sessions and reasons for non-attendance are registered. Readmission to hospital will also be recorded.

### Data analysis and statistical power

The sample size is calculated from a small meaningful change in SPPB, the primary outcome measure [43]. A small meaningful change in the SPPB is mean (SD) 0.5 (1.48) points [44]. With a significance level of 0.05 and power of 80% this estimate requires 140 patients, 70 patients in each group. To compensate for potential drop-outs at least 160 patients will be included in the study. All data will be stored at the research server at the hospital. Between-group differences in normal distributed continuous variables will be analyzed with *t*-tests and/or analysis of covariance (ANCOVA) according to the principle of intention-to-treat (ITT). Missing data will be imputed by carrying the last value forward. Effect sizes will be calculated. To examine relationships correlation and/or multiple regression analyses will be used [45]. The significant level is set to *p* < 0.05.

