## Background

Hip fracture (a fracture of the upper part of the femur), is a worldwide health problem in old age [1, 2]. World-wide, there are approximately 1.7 million hip fractures each year. The highest rates are seen in North America and Europe [1]. In Norway (with 4.7 million inhabitants), about 9000 patients are hospitalized and operated for hip fractures annually. This is among the highest reported hip fracture incidence rates in the world [1–3], even though the hip fracture rates in Norway have declined during the past 15 years. Nevertheless, the forecasted growing number of older people might cause an increase in the absolute number of fractures. This may lead to a substantial, societal, economic and public health burden [4]. Hip fracture is a serious event; one out of every four patients die within one year. Survivors often report severe pain and loss of physical functioning [3].

In a systematic review it was estimated that 42% of survivors after hip fracture did not return to their pre-fracture level of physical functioning, and 35% became incapable of walking independently after the fracture [5]. Moreover, 50% of those able to walk without a walking device before the fracture became permanently dependent on a walking device, and 50% of survivors had persistent loss of independence in daily activities after the fracture [6, 7]. Long-lasting mobility limitations after hip fracture may lead to prolonged physical disability, increased fall risk and new injuries, and 15% of the patients will become permanently institutionalized [7]. Altogether, these impairments cause considerable suffering. Therefore, strategies for hip fracture rehabilitation to enhance the patients’ recovery of physical functioning and prevent future falls is an urgent health care challenge. With such serious consequences, prevention and treatment of fractures to improve outcomes are crucial.

In Norway, the mean length of hospital stay (LOS) after hip fracture surgery is 5–6 days [8]. An increasingly shorter LOS is in line with international studies showing that aging patients are discharged from the hospital “quicker and sicker” [9, 10]. After discharge, most of the patients in Norway are transferred to short-term stays in nursing homes in primary health care before they are able to return to home.

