Running intervention studies for multi-diseased fracture patients with low functional capacity is challenging with regards to data collection. Nevertheless, it is important to run such studies to be able to develop interventions that may improve wellbeing and minimise functional decline in these patients. Prior studies have often used small samples and a pragmatic choice of interventions [13]. The present study has, due to its large sample size and theoretically based intervention, the potential to generate new knowledge that may improve the design of future activity programs for patients with hip fracture. It is our hope that knowledge drawn from this study may contribute to fill the gap between hospital, primary health care and home in the rehabilitation of the frail elderly after hip fracture.

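### The stated 70 patients per group is about half of what the protocol's own inputs require; it gives about 51% power for a 0.5-point SPPB difference, not 80%

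*Protocol article*

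**What the plan says.** All of the calculation stands in the protocol article, section on data analysis and statistical power. The target and its spread are given first: "A small meaningful change in the SPPB is mean (SD) 0.5 (1.48) points". The result follows directly: "With a significance level of 0.05 and power of 80% this estimate requires 140 patients, 70 patients in each group". The allowance for loss comes next: "To compensate for potential drop-outs at least 160 patients will be included in the study".

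The same paragraph describes the analysis as one between groups: "Between-group differences in normal distributed continuous variables will be analyzed with" t-tests and/or ANCOVA, by intention to treat, with the last value carried forward for missing data. The study design section describes a two-arm comparison of additional functional training with usual care alone. The sidedness of the test, a correlation between baseline and follow-up, and the time point that the calculation addresses are not stated.

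**The concern.** The inputs and the result stand in consecutive sentences and do not agree. The article attributes the 140 to the stated estimate alone, so a reader can check it directly, and the check fails for the two-group comparison that the trial is built to make.

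SPPB is the primary outcome, and 0.5 points is the change that the article itself calls meaningful. If power for that difference is near one half, the trial is about as likely to miss it as to find it. A reader who relies on the stated 80% would then give a non-significant result more weight as evidence against an effect than it can carry.

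**Working it through.** **Inputs** (all from the sample size paragraph): difference δ = 0.5; SD σ = 1.48; significance level 0.05, taken as two-sided because no side is stated; power 80%; equal groups; stated n = 70 per group, 140 in total; at least 160 recruited. The standardised difference is 0.5 / 1.48 = 0.338.

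**1. Trying to reproduce the stated 70 per group.** For two independent means the normal approximation is n per group = 2 (z₀.₉₇₅ + z₀.₈₀)² (σ/δ)².

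- Two-sided: 2 × (1.96 + 0.8416)² × (1.48/0.5)² = 2 × 7.849 × 8.762 = 137.5, so 138 per group (276 in total). The exact t-test calculation gives 138.5, so 139 per group (278 in total).
- One-sided 0.05 (t-test): 109.02, so 110 per group (220 in total).

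Neither gives 70. The stated total is 140/278 = 0.50 of the two-sided requirement.

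**2. What does give about 70.** The one-sample or paired formula lacks the factor 2: 7.849 × 8.762 = 68.8, or 70.7 with the t distribution. With n = 70 a one-sample test has 79.6% power. Taking the per-group figure of about 139 as the total would also lead to 140.

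**3. Power of the two-group test at the planned sizes** (two-sided t-test, δ = 0.5, σ = 1.48):

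| Analysed per group | Power |
|---|---|
| 70 (stated requirement) | 51.0% |
| 80 (all 160, no loss) | 56.5% |
| 139 | 80.1% |

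The normal approximation gives 51.5% and 57.0% for the first two rows. A one-sided test at 70 per group has 63.5%.

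**4. Detectable difference.** At 70 per group, 80% power needs a true difference of 0.706 points. The normal approximation is 2.8016 × 1.48 × √(2/70) = 0.70.

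**5. Could ANCOVA be the basis?** The result depends on what 1.48 measures; r is the correlation between baseline and follow-up, assumed here because none is stated.

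- If 1.48 is the SD of a single score, the residual SD is 1.48 √(1 − r²).
- If 1.48 is the SD of a change, then 1.48² = 2σ²(1 − r) with σ now the SD of a score. The residual variance σ²(1 − r²) equals 1.48² (1 + r)/2, so the residual SD is 1.48 √((1 + r)/2).

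| r | Power at 70 per group, 1.48 = SD of a score | Power at 70 per group, 1.48 = SD of a change |
|---|---|---|
| 0.5 | 63% (residual SD 1.28) | 63% (residual SD 1.28) |
| 0.7 | 79% (residual SD 1.06) | 58% (residual SD 1.36) |

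In the second reading at r = 0.7 the requirement is still 118 per group.

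**6. Loss by 12 months, as a scenario only.** Going from 160 to 140 allows 20/160 = 12.5% loss. The Background says of hip fracture in general that "one out of every four patients die within one year". If that applied to this sample, 160 × 0.75 = 120 patients, or 60 per group, would have 12-month data, and power would be 45.0%.

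**The case against.** The strongest defence is that the article allows ANCOVA, and that a fuller protocol may hold a baseline correlation that brings the requirement down to 70 per group. This stands only in part. With r of about 0.7 it works if 1.48 is the SD of a single score. The article attaches 1.48 to a meaningful change, and if it is the SD of change, the same r leaves power at 58%. ANCOVA is also only one of two named options, and the article derives the 140 from the 0.5 and 1.48 without mentioning any adjustment.

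Several stronger readings are tempting, but the documents do not support them:

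- **That a paired formula was used by mistake.** The number fits, but so does a per-group figure taken as the total. The cause is not documented.
- **That the drop-out allowance is wrong because a quarter of patients die within a year.** That figure describes hip fracture patients in general. The trial enrols people who lived at home and excludes those with a life expectancy under 3 months, an MMS-E below 15, inability to walk 10 m before the fracture, or a medical contraindication to training. Its mortality may be lower, while other losses may add to it. The 160 is a minimum, the calculation names no time point, and carrying the last value forward keeps the nominal number analysed, although it adds no 12-month information. The adequacy of 12.5% is a judgement and not an arithmetic error.
- **That the Discussion's description of the study, "The present study has, due to its large sample size and theoretically based intervention", is false.** It follows a remark on small earlier studies and is a comparison with them. The power error does not settle it.
- **That power is lower still because SPPB varies more in this population.** The article gives no SD other than 1.48.

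**Conclusion.** The sample size statement is wrong as written. For the planned between-group comparison, the article's inputs require about 139 per group, and the stated 70 gives about 51% power, some 29 percentage points below the claim. The margin for drop-outs does not repair it, since 160 analysed patients give about 57%.

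This rests on the stated 0.5 and 1.48, equal groups, independent observations and a two-sided 5% test. Making the test one-sided does not change the conclusion. Among the analyses that the article allows, only a baseline-adjusted ANCOVA with r of about 0.7, and with 1.48 read as the SD of a single score, comes close to 80% at 70 per group; the article states neither condition. The 45% at 12 months is a scenario and no part of the finding.

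**What to change.** Rewrite the sample size paragraph so that inputs and result agree:

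- Say that a difference of 0.5 points (SD 1.48) needs 139 patients per group for 80% power with a two-sided 5% two-sample t-test.
- Say that 70 per group gives about 51% power for that difference, and 80% only for about 0.71 points.
- If baseline-adjusted ANCOVA is the intended basis, state the assumed correlation, whether 1.48 is the SD of a score or of a change, and the power that follows.
- Say that a non-significant primary result will be interpreted by its confidence interval, in particular by whether the interval excludes 0.5 points.

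It would also help to name the time point that the calculation addresses and the number expected to have data then, with any mortality figure labelled as an assumption.

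The cost is a few sentences and a less favourable stated power. No extra patients are needed to make the correction.

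### The stated inputs (0.5 SPPB points, SD 1.48, 5% level, 80% power) need about 139 patients per group; the planned 70 give about 51% power in an unadjusted two-sample comparison.

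*Protocol article*

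**What the plan says.** Under Data analysis and statistical power, the Protocol article gives the target and its spread: "A small meaningful change in the SPPB is mean (SD) 0.5 (1.48) points". It then states the result: "With a significance level of 0.05 and power of 80% this estimate requires 140 patients, 70 patients in each group". Enrolment is raised above 140 only to cover losses: "To compensate for potential drop-outs at least 160 patients will be included in the study".

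The same section describes the analysis as a comparison of two groups: "Between-group differences in normal distributed continuous variables will be analyzed with" t-tests and/or ANCOVA. It does not say whether the test is one- or two-sided. It gives no baseline-outcome correlation and no other variance reduction.

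The SPPB is the primary outcome (Primary aim; Primary outcome of physical functioning). The Discussion contrasts the trial with earlier small studies and describes it in these words: "The present study has, due to its large sample size and theoretically based intervention, the potential to generate new knowledge".

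**The concern.** All the inputs to a standard calculation are printed beside its result, so the result can be checked directly. A difference of 0.5 with SD 1.48 is a standardised effect of 0.5/1.48 = 0.338. Seventy per group is far too few to detect an effect that small with 80% power when two independent groups are compared.

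If the figure is wrong, the power claimed for the primary comparison is not delivered. A benefit of exactly the size the protocol calls meaningful could easily be missed. A non-significant result would then be read as coming from an adequately powered trial. The Discussion asks whether this short, early programme is long and intensive enough to have an effect, and an underpowered trial cannot reliably answer no.

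**Working it through.** **Inputs** (all from Data analysis and statistical power): difference 0.5; SD 1.48; significance level 0.05; power 80%; two equal groups. Sidedness is not stated, so two-sided is assumed and one-sided is also tried. Patients are treated as independent.

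**Reproducing the plan's 70 per group with the two-sample formula**

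n per group = 2 × (z₁₋α/₂ + z₁₋β)² × (SD/difference)²

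- Two-sided: 2 × (1.960 + 0.842)² × (1.48/0.5)² = 2 × 7.849 × 8.762 = 137.5, so 138. With the t distribution it is 138.5, so 139 per group and 278 in total.
- One-sided: 2 × (1.645 + 0.842)² × 8.762 = about 108.3. With the t distribution it is 109.0. This is also far from 70.

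Neither version gives 70.

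**Where 70 may come from.** The one-sample or paired formula drops the factor 2: 7.849 × 8.762 = 68.8 (70.7 with the t distribution). This is close to 70. Halving a figure of about 140 per group would give the same number. The article names no formula, so both explanations are inferences and the conclusion does not depend on them.

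**Power at the planned size** (two-sample t-test, two-sided 5%, difference 0.5, SD 1.48)

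| Analysed per group | Power for 0.5 points | Difference detectable with 80% power |
|---|---|---|
| 70 | 51.0% | 0.71 |
| 80 (all 160, no loss) | 56.5% | 0.66 |

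The ratio 0.706/0.5 = 1.41, so the detectable difference at 70 per group is 41% above the target. With a one-sided test, power at 70 per group is about 63%. For 70 per group to be right for 0.5 points, the SD would have to be about 1.05.

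**Baseline-adjusted ANCOVA at 70 per group** (correlations r are assumed; the article gives none)

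- If 1.48 is the SD of the score, the residual SD is 1.48 × √(1 − r²).
- If 1.48 is the SD of a change, the residual SD is 1.48 × √((1 + r)/2).

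| r | Residual SD, score reading | Power | Residual SD, change reading | Power |
|---|---|---|---|---|
| 0.5 | 1.28 | 63% | 1.28 | 63% |
| 0.6 | 1.18 | 70% | 1.32 | 60% |
| 0.7 | 1.06 | 79% | 1.36 | 58% |
| 0.8 | 0.89 | 91% | 1.40 | 55% |

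The two readings move in opposite directions as the correlation rises.

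**The case against.** The strongest reply is that ANCOVA is a named option and the SPPB is measured at baseline. If 1.48 is the SD of the score and the baseline correlation is about 0.7, then 70 per group gives 79% power, essentially what is claimed. A journal article is condensed, and the full protocol might state such a correlation.

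This shows that 51% is the power of the unadjusted comparison and not of every analysis the plan allows. It does not rescue the printed statement. The article attributes the 140 to the 0.5 (1.48) estimate itself, mentions no correlation, and offers ANCOVA only as an alternative to the t-test. The estimate is described as a change, and if 1.48 is the SD of a change, ANCOVA gives only 55% to 63% for correlations of 0.8 down to 0.5. What 1.48 measures depends on a cited source that is not at hand.

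Three smaller points also stand. The one-sample origin of 70 is a guess. The Discussion sentence on sample size compares the trial with earlier ones and states no power, so it is not a second instance of the error. Moving the target to 0.7 points merely because the sample can detect it would have no support in the document, which ties 0.5 to a meaningful change.

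**Conclusion.** The concern holds. On the protocol's own inputs, 70 per group is about half of what 80% power requires: 139 per group two-sided, or about 109 one-sided. Power for 0.5 points is about 51% with 140 patients analysed and about 57% with all 160.

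These figures assume an unadjusted two-sample t-test, a two-sided 5% level and independent patients. Adjustment for baseline would raise power by an amount that depends on the correlation and on what 1.48 measures. Under Randomization and allocation concealment, groups of nursing home departments are allocated, not individual patients, and the calculation makes no allowance for this. Any positive correlation within departments would lower power further. The arithmetic error stands without that point.

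**What to change.** Correct the paragraph under Data analysis and statistical power in one of two ways:

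1. **Keep the size and restate what it delivers.** With SD 1.48 and an unadjusted two-sided test, 70 evaluable patients per group give about 51% power for 0.5 points and 80% power for about 0.7 points; 80% power for 0.5 points would need about 139 per group. Keep 0.5 as the meaningful difference unless a larger one can be justified on its own grounds. Add that these figures assume independent patients.
2. **Base the size on ANCOVA.** Name it as the primary analysis, state the residual SD and the baseline correlation with their source, and give the resulting power.

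In either case, state the sidedness of the test and whether 1.48 is the SD of the score or of the change. It would also help to soften the Discussion's remark on sample size and to say that a non-significant result will be read from its confidence interval against 0.5 points. These last two are advisable but not essential to the correction.

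The cost is one rewritten paragraph and, optionally, one Discussion sentence. No extra patients are needed, but the stated power becomes less favourable. Keeping both 0.5 points and 80% power without adjustment would instead mean about 278 evaluable patients. With the 12.5% loss implied by going from 140 to 160 (1 − 140/160), that is 278/0.875 = 318 enrolled.

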### Time plan of the study

Recruitment will start during spring 2016 and will probably be finished by the end of 2017. The intervention will be ongoing in the same time interval. Data collection will last for 1 year after recruitment. Thereafter, we will write up and publish peer-reviewed articles.

### Ethics and approvals

Before discharge from hospital, an informed consent will be obtained if the physiotherapist who is recruiting is reassured that the patient fully understands what it implies to participate. The patients with increased risk of falls, restrictions in movement or weight-bearing during training and activity will be focused upon to avoid injuries. The nursing staff will be trained to secure the patients properly to avoid falls and dislocations. All patients recruited to the project will also be offered usual care rehabilitation. The study is funded from Vestre Viken Hospital Trust and is approved by the Regional Committee for Ethics in Medical Research (South-East Norway) (2015/2147). ClinicalTrial.cov NCT02780076.

## Discussion

We expect that the intervention described in this protocol will have positive impact on the physical functioning measured by SPPB. The tailored intervention will have potential to promote evidence-based decision-making and empower patients with hip fracture to remain in charge of their own lives. We rely on a systematic approach which corresponds with the guidance on developing and evaluating RCTs [25, 26].

This protocol creates a plan for the investigators to follow. Several issues related to the quality of the study have to be discussed, such as internal and external validity. Internal and external validity relates to whether the results drawn from the study can be trusted and generalized into other contexts. Examples of methodological issues that may influence internal validity in a pragmatic RCT include random allocation, blinding, outcome measures, sample size, drop-outs, statistical methods, and the participants’ adherence to the intervention.

In the present study we are particularly concerned with the outcome measures and the participants’ adherence to the program. A standard set for the measurement of outcomes in patients with hip fracture has been identified [46]. In line with their recommendations we chose to focus on mobility, level of activity, and health-related quality of life measures, and also include some other outcomes, such as pain, fear of falling, number of falls, complications and mortality rate. The intervention is designed to increase the amount of physical activity, which in turn may increase the patients’ physical functioning, such as their ability to move around. Therefore, the primary outcome is physical functioning measured by the SPPB. The SPPB has also been used in prior research to measure effects of interventions on physical functioning. In one study the SPPB was used to examine the effect of comprehensive geriatric care, compared to orthopedic care, in the acute postoperative phase during hospital stay [22]. The SPPB was responsive and able to reveal a difference between the groups even a few days after surgery. Our primary outcome measure is therefore considered to be sensitive to change, responsive and also used in other comparable studies. Our results may therefore be comparable to others, and this will strengthen the validity of the study.

Other outcome measures are also important to apply to give a broad picture of the patients’ health and life situation after hip fracture. The self-reported measurements of activity level and fear of falling will add information on how the patients themselves consider their present activity level and concerns related to future falls. Registration of home care services will give a picture of their ability to manage daily activities. Furthermore, in EQ-5D-5 L the patients’ health-related quality of life, including depression and anxiety, will reveal other important aspects of the recovery of physical functioning after hip fracture. In the present study both performance-based and self-reported outcome measures are used. The different measurements will strengthen the study as they are complementing each other in terms of measuring the functional status in a broad sense [47]. To maximize the test-retest reliability, the assessors are experienced physiotherapists who are properly trained in testing before the inclusion starts.

Gait and balance are important aspects of mobility in everyday life. Moreover, research has shown that functional exercises, which involve shifts between positions with weight-bearing over a changing base of support, are important to improve gait and balance in older people and thereby reduce the fall risk [48, 49]. There is a close association between mortality rate and level of physical functioning, such as mobility [50], which underlines the importance of increased physical activity for the patients with hip fracture. Prior studies have focused on the effect of functional-, strength- and balance exercises several months after hip fracture [13, 16, 29]. To our knowledge, little research has been done on the effect of easily adoptable functional exercises while the patients are at short-term stays in a nursing home after hip fracture. This is a period when the patients have just started their recovery process, but are still vulnerable and in need of support to improve further. In general, exercises are believed to depend on certain intensity with respect to repetitions and exercise duration time to exert their effects. In the meta-analysis of Diong et al [13] they found that the interventions with the best effects were delivered later in the recovery course and with longer duration than the present one. Therefore, it will be interesting to examine whether our functional training intervention, performed 4 times daily for 2 weeks in the early sub-acute phase, is of sufficient length and intensity to exert an effect.

To further take care of the internal validity of the study, an apparent challenge is the adherence to the program. That is whether the patients are capable of adhering to the program and whether the nurses will adhere and keep on initiating the program despite their already heavy workload. We assume that the nurses may get a busier working schedule during the first days of the patients’ short-term stays, but thereafter their workload may be reduced, as the patients get stronger, more mobile and possibly will manage to do functional activities and the functional training by themselves. Even so, adherence to the program is of utmost importance and a challenge that will require motivational efforts from all persons involved.

External validity or generalizability is another important issue to discuss. In this study we include patients who are living at home before the fracture, but are in need of short-term stays after discharge from hospital before they are able to return to home. Those returning directly to home after discharge from hospital are excluded. Also those who are physically or mentally too impaired to manage the training intervention and completing the measurements are excluded from participating. Therefore, the results can only be generalized to a similar group and neither to the healthiest who return directly to home, nor to those that were institutionalized before the fracture.

The present experimental intervention is considered to be a complex intervention. A complex intervention in health care is defined according to the number of interacting components involved [51]. The outline for the arguments in this protocol is organized according to the guidelines of the Medical Research Council (MRC) guidance on how to develop and evaluate complex interventions [51]. According to the new Medical Research Council guidance, certain issues have to be taken into account when reporting such interventions. The different components within the interventions, how the intervention is tailored to the local context, and how the intervention is implemented are all important factors to describe in detail. A description of these elements may broaden the understanding of possible other active components within the intervention and thereby add knowledge to factors that may have contributed to the eventual effect [26]. These issues are taken into consideration and elaborated on when reporting on the effects from the randomized controlled trial, but are not included in this protocol.

Running intervention studies for multi-diseased fracture patients with low functional capacity is challenging with regards to data collection. Nevertheless, it is important to run such studies to be able to develop interventions that may improve wellbeing and minimise functional decline in these patients. Prior studies have often used small samples and a pragmatic choice of interventions [13]. The present study has, due to its large sample size and theoretically based intervention, the potential to generate new knowledge that may improve the design of future activity programs for patients with hip fracture. It is our hope that knowledge drawn from this study may contribute to fill the gap between hospital, primary health care and home in the rehabilitation of the frail elderly after hip fracture.

